### Intervention

The implementation team of the intervention process includes a sports rehabilitation physician, a neurologist, a volleyball coach, a graduate student, and 2 undergraduate students. Before the formal intervention, the researchers were made familiar with the intervention equipment and intervention process through training. A between-group control design will be used with the same interventions. The 3 groups of participants will receive the same visual-motor response training for 30 minutes a day over 14 days. Response training will be completed with the help of gForceDual equipment and Neuro Rehab System (OYMotion). The participants download the Neuro Rehab System–based app and connect the gForceDual device to their mobile device through Bluetooth. During each training session, the gForceDual equipment will be secured to the transverse striation of the distal wrist of the participants’ right upper limb, and its electrode will be attached to the ventral part of the palmar longus muscle, brachioradialis muscle, radial carpal flexor muscle, and ulnar carpal flexor muscle. The response sensitivity will be adjusted via the app, and the participants will be guided by visual information to carry out wrist dorsal extension and flexion. The speed adjustment function in the app will be set to divide the training speed into gears, with a total of 10 gears. The default setting is sixth gear during the intervention. If an older person cannot keep up with the response, the app will downshift through gears; conversely, if an athlete can adapt well to a high gear, the app will upshift the gear. The researchers will record electromyographic signals produced by dorsal extension and flexion of the wrist.

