## Methods

### Study Design

This is a prospective, single-center, open-label, controlled clinical trial conducted between January 2022 and December 2025. This study will recruit professional volleyball players, ordinary college students, and older people without any professional sports training. In total, 78 participants will be recruited at the Shanghai University of Traditional Chinese Medicine, China, via the university website or posters, with 26 participants in each group. All participants will undergo baseline assessments, including acousto-optic response time tests and fMRI scans. This will be followed by 2 weeks of visual-motor response training. After 2 weeks, the outcomes of the intervention will be evaluated (Figure 1).

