### Outcome Measures

The aim of the study is to explore the functional characteristics of brain perceptions of movement and the cognitive changes in different groups after response ability training. The primary outcome is defined by differences in fMRI images of characteristic areas of the brain before and after the intervention. A Siemens Magnetom Verio 3.0T MRI system will be used for scanning before and after the intervention.

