## Discussion

### Principal Findings

This paper presents the protocol for a single-center, open-label, controlled clinical trial that will evaluate the effects of combined visual-motor response training on cognitive function to help patients recover and maintain quality of life. We aim to directly test the hypotheses that the perceptual-motor system of the brain of people with long-term exposure to combined visual-motor response ability training has a functional advantage compared to the general population and that combined visual-motor response ability training is effective in improving cognitive functioning in both the general population and the aging population. In addition, the trial will evaluate the effectiveness and safety of exercise-based nonpharmacological therapies when applied to improve cognitive function. This study highlights the importance of finding novel therapies for cognitively impaired populations. The implementation of exercise-based, nonpharmacological therapies is a potential option with profound implications for managing chronic diseases and improving health care in an aging society.

Advanced cognitive functions, such as cognitive flexibility, working memory, and long-term memory, tend to decline with age after the age of 20 [26]. Cognitive aging is usually accompanied by atrophy in brain structures such as the caudate nucleus, cerebellar hemisphere, lateral prefrontal cortex, and hippocampal gyrus [27]. The results of several randomized controlled trials have shown that combined exercise and biofeedback-based training are effective in ameliorating cognitive impairment and improving physical functioning, memory, and executive function [28-31]. However, Griffen et al [32] confirmed through a randomized controlled trial that resistance exercise does not significantly improve cognitive function [32]. Other studies have had similar results, indicating that while exercise may improve overall cognitive functioning, it primarily enhances executive ability, with minimal impact on memory and social cognition [33,34]. Unlike the general population and the older population, improvements in cognitive functioning have long been demonstrated in athletes undergoing combined exercise and biofeedback training [35-37]. Therefore, differential findings prompted us to explore the effectiveness of visual-motor response training.

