fMRI locates complex cognitive activities in the brain with high spatial resolution, providing a more accurate and objective view of brain information processing during exercise and identifying the brain regions involved in effective and reasonable information processing. ALFF is a relatively stable metric in fMRI sequences that responds to the low-frequency electrical activity of local neurons in the resting state [38]. ALFF and ReHo are used to identify neural networks throughout the brain [39]. Based on the assumption that a voxel is similar to its neighboring voxels over time, neural networks can be identified by evaluating and comparing the synchronization or similarity over time between each voxel in the region of interest and its neighboring voxels [39,40]. Unlike previous studies, we will not only use questionnaires and scales to assess the cognitive function of patients but also assess the changes in the functional structure of the brain by fMRI, which will make the evidence of the study more explicit. This exploratory study will attempt to open new horizons for subsequent trials. If the hypothesis is valid, combined visual-motor response ability training will replace exercise-only interventions as a new preventive measure and treatment method, which is significant for the current society with an aging population.

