### Strengths and Limitations

The study has some strengths. First, it used visual-motor response training rather than an exercise-only intervention, aiming to increase biofeedback and identify more effective measures for improving cognitive function. Second, we intervened with 3 groups with different training bases, physical functioning, and cognitive functioning to provide a broader perspective on the effectiveness of the intervention. In addition, this study simultaneously assessed changes in psychological status and functional brain imaging, providing a broader evidence base for the efficacy of the intervention. However, the study has some limitations. First, the study’s intervention period is short, and it will not be known whether the intervention effect is significant over a 2-week period. The lack of randomized assignment in the study is also a limitation, as it can potentially affect the accuracy of the findings. Therefore, further studies with high evidence quality should be conducted in the future to better explore the efficacy of combined visual-motor response ability training.

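### All three groups are trained and only population and time are analysed, so the trial cannot attribute pre-post change to the training or support its efficacy and replacement statements

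*Protocol article*

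**What the plan says.** The title, abstract and Study Design section call this a controlled trial. The Intervention section explains the term: "A between-group control design will be used with the same interventions". It continues: "The 3 groups of participants will receive the same visual-motor response training for 30 minutes a day over 14 days". The groups are existing populations, "with 26 participants in each group" (Study Design).

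The primary outcome is "differences in fMRI images of characteristic areas of the brain before and after the intervention" (Outcome Measures). Reaction time, the MMSE and the 10-word test are secondary outcomes, measured at the start and end of the 2 weeks. The Statistical Analysis section specifies a two-way repeated-measures ANOVA. Its between-subject factor is population (athletes, young, older) and its within-subject factor is time (before, after). Treatment is not a factor.

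Three statements go beyond population differences:

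- The third aim in the Introduction is a preliminary confirmation of efficacy and safety.
- Principal Findings says the study will directly test that "combined visual-motor response ability training is effective in improving cognitive functioning in both the general population and the aging population".
- The same section says that, if the hypothesis is valid, "combined visual-motor response ability training will replace exercise-only interventions as a new preventive measure and treatment method".

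Strengths and Limitations names the short intervention period and says "The lack of randomized assignment in the study is also a limitation". It does not mention that no participant goes untrained or does exercise only.

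**The concern.** To say that training improves cognition, one must compare what happened with training to what would have happened without it. This design observes only the first. Scores on reaction time, word recall and the MMSE can rise at a second sitting 2 weeks later because the task is familiar. In an open-label study they can also rise because participants expect to improve. A significant time effect would be open to all of these explanations, yet under the stated hypothesis it would probably be reported as evidence of effectiveness.

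The interaction does not fill the gap. It asks whether the populations change by different amounts. If training helped all three equally, which would be a good result for the second hypothesis, the interaction would show nothing.

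Any statement relative to exercise-only programmes has no data behind it, because nobody in the trial follows one.

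**Working it through.** **What each term in the planned ANOVA estimates.** Write the mean change in group g as T_g + R_g, where T_g is the effect of training and R_g is everything else that shifts scores between the two sittings (practice, expectation).

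- Time main effect: the average of (T_g + R_g). T and R always appear as a sum, because no group has T = 0 by design.
- Group by time: differences between groups in (T_g + R_g). If T is the same in every group it cancels.
- Baseline group comparison: does not involve T or R, so it is unaffected.

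**How often retest gain alone would look like an effect.** The document gives no figure for retest gain, so there is no figure of the plan's own to reproduce. The inputs are:

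- from Sample Size: 20 per group before allowance for loss, 60 in all;
- from Statistical Analysis: two-sided alpha of .05 for these outcomes;
- assumed: T = 0, retest gain 0.3 to 0.5 SD of the raw score, test-retest correlation r of 0.5 to 0.7.

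The SD of a change score is SD × √(2(1 − r)), so the standardized change is dz = gain / √(2(1 − r)). Rejection rates come from the noncentral t for the paired test (19 df, noncentrality dz√20) and the noncentral F for the time effect (1 and 57 df, noncentrality 60·dz²).

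| Gain (SD) | r | dz | Paired test, n = 20 | Time effect, N = 60 |
|---|---|---|---|---|
| 0.3 | 0.5 | 0.3/√1.0 = 0.30 | 25% | 63% |
| 0.3 | 0.7 | 0.3/√0.6 = 0.39 | 38% | 84% |
| 0.5 | 0.5 | 0.5/√1.0 = 0.50 | 56% | 97% |
| 0.5 | 0.7 | 0.5/√0.6 = 0.65 | 78% | 100% |

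The rate without any gain would be 5%. If all enrolled participants were analysed, the ranges would be 31% to 89% (n = 26) and 74% to 100% (N = 78). At the .01 level that the plan uses for functional connectivity and for the post hoc mask, the same assumptions give 9% to 52% (n = 20) and 38% to 99% (N = 60). That line shows sensitivity to alpha only. It is not an estimate for imaging, because the assumed gains concern behavioural tests.

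**Whether the interaction can see a common effect.** In 20,000 simulated trials with 20 per group and a true training effect of 0.8 SD of change in every group, the interaction was significant in 5.2%, which is its null rate.

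**Statements set against the design.**

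| Statement | Comparison it needs | Available? |
|---|---|---|
| Aim 1: differences between populations | Population vs population | Yes |
| Different change in different populations | Group by time | Yes, under adapted training speed |
| Efficacy aim and effectiveness hypothesis | Trained vs untrained | No |
| Replacement of exercise-only programmes | Trained vs exercise only | No |

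**The case against.** The best defence is that the article is modest about itself. It calls the study exploratory under Sample Size and again in the Discussion, words the efficacy aim as preliminary, concedes non-randomization and asks for stronger studies to follow. It also discloses what its control consists of. Aim 1 and the first hypothesis compare populations, and the planned factors suit them. All of this stands, and it limits the point to the efficacy aim, the second hypothesis, the replacement remark and the label. It does not remove the point. Exploratory status does not supply a comparator. Non-randomization is a different limitation, since here there are no differing treatments to which anyone could have been randomized. An analysis plan not shown could not create the missing group either.

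Some stronger readings are tempting but not supported:

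- *That the trial plans to conclude superiority over exercise.* The replacement sentence is a conditional remark in the Discussion. The Conclusions section says only that the study may provide an effective therapy. The objection is that the condition cannot be tested here and that, even if met, it would say nothing relative to exercise.
- *That regression to the mean inflates the change.* This needs selection on an extreme value of the outcome. The eligibility criteria state no such cut-off. ADL is used for screening, but no threshold is given.
- *That the Intervention section contradicts itself on exposure.* It describes the same training and then says "If an older person cannot keep up with the response, the app will downshift through gears", with upshifting for athletes. One programme with a common default gear and an adaptive speed rule can be read coherently. What follows is a matter of interpretation: the interaction compares populations whose training speed may differ.
- *That the percentages above apply to the primary outcome.* They do not. The document offers no basis for a retest shift in ALFF, ReHo or connectivity.

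**Conclusion.** The point holds in this limited form. That there is no untrained or exercise-only comparator follows directly from the text and needs no assumption, nor does the conclusion that the time effect cannot be attributed to training and the interaction cannot see a common effect. The label *controlled*, the claim to test effectiveness directly, the preliminary efficacy aim and the replacement remark therefore exceed what the design can show. Baseline differences between populations and differences in pre-post change remain legitimate results.

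The size is illustrative. False attribution rates of 25% to 78% (one group of 20) and 63% to 100% (60 participants) rest on an assumed retest gain and correlation, a zero training effect, behavioural outcomes and alpha .05. The size for the fMRI primary outcome is unknown; the problem of attribution applies to it in kind.

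**What to change.** Recruitment was complete by September 11, 2024 (Results), so the practical remedy lies in wording and reporting:

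1. Describe the trial as an uncontrolled pre-post study in three populations, and drop *controlled* from the title and text.
2. Limit conclusions to baseline differences between populations and differences in pre-post change.
3. Add to the limitations that there is no untrained or exercise-only comparator, so time effects are not attributable to training.
4. Reword the efficacy aim and the second hypothesis as exploration of pre-post change.
5. Remove the statement about replacing exercise-only interventions.
6. Interpret the group by time result as differential change under individually adapted training speed, and report the gear reached if it is recorded. The article does not say whether the app stores it.

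The cost is editing, plus one descriptive table if gear data exist. No planned test changes. The downside is weaker claims; an efficacy claim would need a later study with a concurrent comparator.

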### Outcome Measures

The aim of the study is to explore the functional characteristics of brain perceptions of movement and the cognitive changes in different groups after response ability training. The primary outcome is defined by differences in fMRI images of characteristic areas of the brain before and after the intervention. A Siemens Magnetom Verio 3.0T MRI system will be used for scanning before and after the intervention.

Adverse events are defined as any adverse experience that may be related to the trial treatment procedure that occurs during the course of the study. Any discomfort reported by the participants during the study will be carefully recorded.

### Safety Measures

An excessively high gear or initial discomfort may cause dizziness, nausea, or fatigue in some participants during the audio-visual response training. During the training, research assistants will monitor the participants’ status and provide medical assistance as needed. If a participant is unable to adapt to our training model, the training session will be promptly terminated, and follow-up medical counseling and assistance will be offered.

### Statistical Analysis

All variables that can be measured directly will be analyzed descriptively by tabulating the empirical distributions. For continuous variables, mean (with SD), median, minimum, and maximum values will be documented. Classification variables will be recorded as incidence and percentage. Measurement data following a normal distribution will be analyzed with a 2-way repeated measures ANOVA. For intergroup factors, the participants will be divided into 3 groups, comprising athletes, young people, and older people. The intragroup factor will be evaluation time, which has 2 levels—before and after the intervention. The main effects and interactions among the 3 groups will be analyzed. For nonnormally distributed data, the Wilcoxon symbolic rank test will be used for intragroup analysis, and the Mann-Whitney *U* test will be used for intergroup comparison. The significance level of the statistical test is set at α=.05, and bilateral tests will be carried out. Differences in classification variables will be calculated using the *χ*^2^ test. *P*<.05 will be considered statistically significant.

The differences in brain fMRI images will be analyzed by MATLAB (R2014a; MathWorks) and Statistical Parametric Mapping (version 12; UCL Queen Square Institute of Neurology) [24]. Based on the intergroup analysis of the resting-state amplitude of low-frequency fluctuations (ALFF) and regional homogeneity (ReHo) indices, we will perform a flexible-design ANOVA to characterize the individual samples at each time point. Analyses will include time main effects, grouping main effects, time × grouping interactions, and statistical parameter diagrams. The post hoc test mask will reflect differences in brain regions where *P*<.01 and voxel >10, as determined by the ANOVA results. The intergroup analysis of functional connections will be done using GRETNA (Neuroimaging Tools and Resources Collaboratory) [25]. The functional connection differences among the 3 groups will be analyzed with a 2-factor repeated measurement ANOVA, and the intragroup analysis will be conducted with a paired 2-tailed *t* test. A *P* value <.01 is considered to show statistical significance. BrainNet Viewer (Neuroimaging Tools and Resources Collaboratory) will be used to draw schematic maps of brain regions with significant differences.

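### For non-normal secondary outcomes the plan names a two-sample test for three groups and no counterpart to the group × time interaction that it specifies for normal data

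*Protocol article*

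**What the plan says.** All of this is in the protocol article, Methods, Statistical Analysis, first paragraph.

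- **Between-group factor.** "For intergroup factors, the participants will be divided into 3 groups, comprising athletes, young people, and older people".
- **Within-participant factor.** "The intragroup factor will be evaluation time, which has 2 levels—before and after the intervention".
- **Normal data.** "Measurement data following a normal distribution will be analyzed with a 2-way repeated measures ANOVA". On what this ANOVA tests: "The main effects and interactions among the 3 groups will be analyzed".
- **Non-normal data, change within a group.** "For nonnormally distributed data, the Wilcoxon symbolic rank test will be used for intragroup analysis".
- **Non-normal data, differences between groups.** Here "the Mann-Whitney *U* test will be used for intergroup comparison".
- **Threshold.** "The significance level of the statistical test is set at α=.05, and bilateral tests will be carried out".

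The second paragraph of the section treats imaging separately. ALFF and ReHo get an ANOVA with a time × grouping term, and functional connectivity gets a two-factor repeated measures ANOVA. The rule for non-normal data therefore concerns the non-imaging secondary outcomes listed under Outcome Measures: reaction time, HAM-D, HAM-A, MMSE, ADL, SCD-Q9 and the 10-word memory test.

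**The concern.** Mann-Whitney compares two samples. With three groups it can only be run pair by pair, and the only threshold given is .05 for each test.

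The normal-data route tests whether change differs between groups. The non-normal route names nothing that does so. A distributional check on each outcome would then decide not only which test is used but which question is answered. The second aim at the end of the Introduction, and the Abstract's conclusion about comparing improvements across populations, both need a comparison of change between groups.

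The input to the Mann-Whitney test is also left open. Under Inclusion Criteria the young groups are aged 18–23 and the older group 55–70, and the Discussion says advanced cognitive functions tend to decline after age 20. A between-group test on post scores would pick up differences that existed before training.

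**Working it through.** **Inputs.** From the protocol: 3 groups, 2 times, two-sided α = .05 (Statistical Analysis); 20 analysable and 26 recruited per group (Sample Size). The protocol gives no error rate for this rule to reproduce, so the benchmark is its nominal 5%. It gives no standardised within-group change and no baseline difference for any scale; both are assumed below and shown as ranges.

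**1. Number of tests.** Three groups give 3 × 2 / 2 = 3 pairs per outcome.

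**2. Familywise error when all three groups are equal.** If the three tests were independent, the error would be 1 − 0.95³ = 0.143. Pairs share a group, so the tests are correlated and the true figure is lower. Simulation with 10,000 trials per setting, normal and lognormal data:

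| Procedure | Chance of at least one false positive |
|---|---|
| Three unadjusted Mann-Whitney tests, n = 20 | 12.1–12.3% |
| Three unadjusted Mann-Whitney tests, n = 26 | 11.5–12.3% |
| Kruskal-Wallis, n = 20 or 26 | 4.5–5.3% |
| Holm over the three pairs, n = 20 or 26 | 3.8–4.3% |

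**3. Mann-Whitney on post scores.** Assume that the older group starts 0.5–1.0 SD lower, that all groups change equally, and that n = 20. At least one older-versus-young comparison is then significant in 47–94% of trials, although training worked equally in all groups. Kruskal-Wallis on change flags about 5%.

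**4. Separate Wilcoxon verdicts compared across groups.** Suppose all groups truly change by the same amount and each test has power p. The chance that at least one group is significant and at least one is not is

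1 − p³ − (1 − p)³,

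which peaks at 1 − 2 × 0.5³ = 0.75 when p = 0.5. Simulated Wilcoxon power with normal change scores gives:

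| Assumed standardised change | n = 20: power | n = 20: disagree | n = 26: power | n = 26: disagree |
|---|---|---|---|---|
| 0.1 | 0.07 | 19% | 0.08 | 21% |
| 0.3 | 0.24 | 54% | 0.30 | 63% |
| 0.4 | 0.38 | 71% | 0.48 | 75% |
| 0.5 | 0.54 | 75% | 0.67 | 67% |
| 0.6 | 0.70 | 63% | 0.82 | 44% |
| 0.8 | 0.91 | 24% | 0.97 | 9% |
| 1.0 | 0.985 | 4% | 0.998 | 1% |

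Worked example, n = 20, change 0.5: 1 − 0.541³ − 0.459³ = 1 − 0.158 − 0.097 = 0.745.

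Kruskal-Wallis on the change scores rejected in 4.3–5.5% of trials in every equal-change setting simulated (standardised change 0 and 0.3–0.6, both sample sizes).

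**The case against.** **Only secondary outcomes are involved.** This stands. The primary outcome is fMRI, with its own time × grouping analysis, and the study calls itself exploratory. A reader might infer that the main analysis is compromised; the document does not support that.

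**The inference that the plan never tests group × time.** A reader might conclude this, but it goes too far. Mann-Whitney applied to change scores would test difference in change, pair by pair. The text does not say so, and it does not rule it out. What can be said is that no such test is named.

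**Adjustment may be in an unseen analysis plan.** This stands in part. Silence on adjustment alone would not be a finding for a condensed article. Naming a two-sample test for three groups, and dropping an interaction that is specified two sentences earlier, is a choice the article makes itself.

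**The numbers do not all apply to one reading.** This stands. The 11–12% requires all three groups to be equal. On post scores with an older-group deficit, only the athlete–student comparison is a true null, and its error is about 5%. The 11–12% therefore bears mainly on change scores, and the confounding bears on post scores.

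**The 75% is a worst case.** This stands. It is the mathematical maximum, reached near 50% power, and it falls to 1–4% for a large common effect. The protocol also never says that verdicts will be compared across groups. The figure shows only that such a comparison cannot replace an interaction test.

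**The fallback may seldom be used.** The document gives no distributional data. Floor or ceiling clustering on bounded scales in healthy volunteers is plausible, but it is an assumption.

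**Within-group change is also a hypothesis.** This stands. The Discussion hypothesises that training works in both the general and the ageing population, and Wilcoxon tests that directly.

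**Conclusion.** The point holds for non-normal, non-imaging secondary outcomes and should be fixed. The rule names a two-sample test for three groups and no counterpart to the interaction specified for normal data, and it leaves the compared quantity undefined.

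The size depends on how the rule is carried out:

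- Three unadjusted pairwise tests have a familywise error of about 11–12% instead of 5%, if all three groups are equal.
- Tests on post scores confound baseline age differences with training effects; the extent depends on an unstated baseline gap.
- Wilcoxon verdicts compared across groups with equal true change disagree in about 4–75% of trials at n = 20 and 1–75% at n = 26, over an assumed standardised change of 0.1–1.0.

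How many outcomes are affected depends on how many prove non-normal, which the document does not allow one to predict.

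**What to change.** Replace the sentence on non-normal data with a rule along these lines:

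1. Test group × time with Kruskal-Wallis on each participant's post-minus-pre change.
2. Follow with pairwise Mann-Whitney tests on the change scores, Holm-adjusted over the three pairs.
3. Keep Wilcoxon signed-rank for change within each group, and state that differences between groups are not inferred from which groups reach significance.
4. Judge normality on model residuals or change scores, not on raw values pooled over three different populations.

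The change is to analysis wording only; no data, visits or sample size are affected. The price is slightly less liberal pairwise tests. The article expected data collection and analysis to finish by February 2025. If the analysis is still open, make the change beforehand; if not, report it as a documented departure from the published rule.
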